### Sample size

The sample size expected for the current study is ‘fixed’ and has been previously estimated at between 400 and 500 CAP patients per calendar year [31]. The accrual period will be 24 months. Assuming that 70 % of patients in the control arm will achieve the primary outcome of being discharged alive from hospital, and setting power = 0.8 and statistical significance (two-sided) α = 0.05, the detectable ASP-i effect size is estimated to be up to an approximately 20 % reduction in length of stay [32]. The *stpower cox* command in STATA/MP 13.1 for Mac will be used for the calculation. 

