### Antimicrobial stewardship

Antimicrobial stewardship is defined as any intervention that minimizes unwarranted variation in antimicrobial utilization from evidence-based best practice with the intent of improving patient safety and quality of care [19]. ‘Unwarranted’ refers to the absence of patient- or disease-specific reasons to justify practice variation from evidence-based practice standards. Antimicrobial stewardship can be operationalized in many different ways, but prospective audit and feedback (persuasive approach) and restricted antimicrobial prescribing policies (restrictive approach) appear to be the most efficacious interventions to achieve the goals of antimicrobial stewardship [19, 20]. Antimicrobial stewardship programs (ASPs) have demonstrated efficacy in improving antimicrobial prescription and reducing rates of hospital-acquired infections [20]. Antimicrobial stewardship programs directed at CAP patients have demonstrated reductions in mortality [15, 21], but have failed to demonstrate reductions in length of stay [20]. Of note, the study by Fine *et al*. [22] used a cluster randomized controlled trial design to examine the impact of an ASP on length of hospital stay in CAP patients. This was the only study to model length of stay as a time-to-event occurrence; differences between the length of stay in intervention and control groups were assessed by survival analysis. The intervention consisted of a prospective chart audit starting on day 3 of hospitalization and physician feedback in the form of a recommendation suggesting the optimal timing of conversion from intravenous to oral antibiotics. The intervention was modeled as a time-invariant dichotomous variable in the final model, despite the fact that the timing of the recommendation varied by up to 7 days from the time of enrollment. The hazard ratio for discharge was 1.16 (95 % confidence interval, 0.97–1.38) for the intervention group, suggesting a non-significant reduction in length of stay of 16 %. It is unknown whether this hazard ratio would have reached statistical significance if the intervention was modeled as a time-dependent covariate in the final model, as unaccounted-for time-dependent bias might have diluted the final intervention effect point estimate [23].

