### Study design

This is a pragmatic controlled non-randomized clinical study intended to measure the effectiveness of a ‘real-world’ program [27]. The ASP-i will be implemented in a modified stepped-wedge design [28]. Baseline patient data will be collected for all enrolled patients on each of the medical wards for the first 3 months of the study, and then the ASP-i will be introduced to each medical ward in a non-randomized sequential fashion in 2-month intervals until all medical wards are exposed to the intervention. This design was chosen for several reasons; the preponderance of evidence suggests that antimicrobial stewardship interventions are beneficial to patient safety and quality of care [29]; there are human resource limitations in rolling out the program simultaneously to all wards; and the design has the advantage of a contemporaneous control group for comparison. The unit of randomization in this study could have been the four medical wards; however, randomization of the wards was not included in the design. The allocation of CAP patients to one of the four medical wards is controlled by bed allocation, an administrative branch of the hospital. Bed allocation was blinded to the study and the process of patient allocation is solely dependent on bed availability. In addition, the patients, regardless of their ward location, were all admitted to the hospitalist service. The hospitalist service provides coverage across all four medical wards and has no influence on the allocation of patients to any of the wards. In essence, the patients will be ‘naturally’ allocated to one of the four medical wards and one of the attending hospitalists by a bed allocation process that is blinded to the intervention, so that the additional randomization of the wards themselves should provide very little benefit with respect to minimizing selection bias. In addition, the four medical wards can all accommodate patients with CAP; however, one of the medical wards has historically accommodated more CAP patients than the other three. As a result, this ward was chosen as the first ward to receive the ASP-I, as this would ensure that the maximum number of CAP patients would have earlier access to the ASP-i. The ethical principle of utilitarianism was used to guide the order of ward exposure to the ASP-i. The target of the intervention is the most attending physician (hospitalist) , while the unit of analysis will be individual patient outcomes adjusted for potential clustering effects within hospital wards.

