### Statistical methods

An extended Cox regression analysis that models the ASP-i as a time-variant covariate will be used to compare the primary and secondary outcome measures between the control and intervention groups [34]. Violations of the proportional hazards assumption for each covariate will be identified using the method of Schoenfeld residuals combined with the graphical method of log-log survival curve analysis [34]. Results will be reported as hazard ratios with 95 % confidence intervals. Patients who remain in hospital beyond 14 days will be administratively censored. Competing events, such as death or transfer from a medical ward to a critical care unit will be assumed to be non-informative conditional on the covariates included in the final model [34]. Time to ASP-i will be modeled as a time-variant covariate in the final model to account for any time-dependent bias [23]. The ASP-i exposure will be coded as a dichotomous variable; 0 = no ASP-i, switching to 1 = ASP-i at the time of the ASP-i and remaining 1 throughout the remainder of the follow-up time. This method treats a patient who has received an ASP-i as a non-ASP-i patient prior to the intervention. Other variables known to be associated with the primary and secondary outcome measures will also be included in the final model [5], and include; age, sex, Charlson comorbidity index, CURB-65 score, time (days) to clinical resolution, and complications from pneumonia, such as empyema. Fixed effects of wards on the outcomes will accounted for by including them as indicator variables in the final model. Maturation of ASP-i effect on outcomes over time will be adjusted by including a categorical time variable in the final model (time variable will be defined as ‘quarter’ from start of study). A dichotomous variable for acceptance or rejection of the ASP-i will be part of an interaction term with the control/intervention group variable to permit a per-protocol analysis. Sensitivity analysis will be done using a competing events Cox regression model to determine the impact of the assumption of the non-informative nature of events, such as death and admission to an intensive care unit [35].

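### The stated 80% power for about a 20% shorter stay assumes an even exposure split unrelated to ward or calendar time; the planned model gives roughly 43–68%

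*Protocol article*

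**What the plan says.** The Sample size section of the protocol article treats the sample as fixed, at "between 400 and 500 CAP patients per calendar year". It adds "The accrual period will be 24 months", which gives 800–1,000 patients. For the event rate it assumes that "70 % of patients in the control arm will achieve the primary outcome of being discharged alive from hospital". Power and significance level are the usual ones: "setting power = 0.8 and statistical significance (two-sided) α = 0.05". From these inputs it concludes that "the detectable ASP-i effect size is estimated to be up to an approximately" 20%, as a shortening of the stay. It names the Stata power routine for Cox models. It gives no hazard ratio, no exposed/unexposed split and no allowance for correlation between exposure and other covariates.

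The rest of the article fixes the exposure and the model:

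- Study design: a three-month baseline on all four wards, after which "the ASP-i will be introduced to each medical ward in a non-randomized sequential fashion in 2-month intervals until all medical wards are exposed". Here and under Assignment of intervention, the ward with most pneumonia patients goes first.
- Intervention and Participant timeline: only patients who meet the review criteria receive the intervention, from 48 hours after admission at the earliest. Follow-up is censored at 14 days.
- Statistical methods: exposure is a 0/1 variable that switches at the patient's own review. "Fixed effects of wards on the outcomes will accounted for by including them as indicator variables in the final model", and calendar quarter enters as a categorical term.

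The Antimicrobial stewardship section reads a hazard ratio for discharge of 1.16 in a cited trial as "suggesting a non-significant reduction in length of stay of" 16%.

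**The concern.** The power figure appears to belong to a simpler study than the one described. A Cox power calculation depends on how evenly exposure is split and on how much of its variation remains after adjustment. Here exposure cannot occur on a ward before it switches and becomes common afterwards, so it is tied to ward and, above all, to quarter. Discharges before 48 hours cannot carry any contrast between exposed and unexposed patients. Both features reduce the information available.

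At stake is how a non-significant result is read. A reader who trusts the sentence would take it as fair evidence against a 20% shorter stay, although the planned model would miss an effect of that size about one time in three at best and more than half the time at worst. The phrase 'up to' adds to the problem: with a fixed sample, the figure at 80% power is the smallest effect detectable, not the largest.

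**Working it through.** **Formula.** With E events, exposed share p, and R² for the regression of exposure on the other covariates, the detectable hazard ratio at 80% power and two-sided 5% is exp{2.8016 / √[E·p(1−p)(1−R²)]}. Power at HR 1.25 (ln 1.25 = 0.2231) is Φ{0.2231·√[E·p(1−p)(1−R²)] − 1.96}. Under a constant discharge hazard, the reduction in stay is 1 − 1/HR.

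**1. Reproducing the stated figure.** Take p = 0.5 and R² = 0.

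| Patients | Events (70%) | Detectable HR | Shorter stay | Power at HR 1.25 |
|---|---|---|---|---|
| 800 | 560 | 1.267 | 21.1% | 75% |
| 900 | 630 | 1.250 | 20.0% | 80% |
| 1,000 | 700 | 1.236 | 19.1% | 84% |

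The midpoint matches almost exactly, so these are very probably the inputs, although the article does not state them.

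**2. When wards switch.** The wards switch at months 3, 5, 7 and 9 of 24.

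- Equal wards: the control-phase share is (3+5+7+9)/96 = 25%.
- Assumed ward shares 40/25/20/15, busiest first: (0.40×3 + 0.25×5 + 0.20×7 + 0.15×9)/24 = 5.2/24 = 21.7%.

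Regressing ward-month phase on ward and quarter indicators gives R² of about 0.75 (equal wards) or 0.74 (40/25/20/15). Quarter alone accounts for about 0.69–0.70. With 40/25/20/15, the variance of phase left after adjustment is 0.0442.

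**3. From ward phase to the planned exposure.** Suppose 60% of eligible patients on switched wards are reviewed (assumed).

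- Exposed share: 0.6 × 0.783 = 0.47.
- Residual variance: 0.6² × 0.0442 + 0.783 × 0.6 × 0.4 = 0.204.
- R²: 1 − 0.204/(0.47 × 0.53) = 0.18.
- 900 patients, all 630 events counted: √(630 × 0.204) = 11.3, so HR 1.28 and power about 71%.

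**4. Removing discharges before 48 hours.** With a constant hazard and 70% discharged by day 14 (assumed), 1 − 0.3^(2/14) = 15.8% leave before 48 hours. That is 0.158/0.70 = 22.6% of events, which leaves 488 of 630.

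- 900 patients: √(488 × 0.204) = 9.98, so HR 1.32 (24–25% shorter) and power about 60%.
- 1,000 patients: 542 events, √(542 × 0.204) = 10.5, so HR 1.31 (about 23% shorter) and power about 65%.

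**5. Simulation of the planned model.** This used time-varying exposure from 48 hours, ward and quarter terms, ward shares 40/25/20/15, and power taken from the mean standard error.

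| Reviewed (assumed) | Power at HR 1.25, N = 900 | Power at HR 1.25, N = 1,000 |
|---|---|---|
| 40–80% | 56–64% | 60–68% |
| 95% | about 43% | about 46% |

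Across these cases the detectable HR is about 1.29–1.42, so the stay is 1 − 1/1.29 = 22.5% to 1 − 1/1.42 = 29.6% shorter. The hand calculation in step 4 falls inside these ranges.

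**6. Lower bound.** Take a pure ward-phase contrast with 900 patients and equal wards: √(630 × 0.25 × 0.75 × 0.25) = 5.43, so HR 1.67 and power 23%. Across the formula and simulated standard errors, power is about 22–29%.

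**The case against.** The strongest reply is that exposure is coded per patient and per moment, not by ward phase. Unreviewed patients, and time before review, on switched wards count as unexposed. At 60% review the split is close to even and R² is about 0.18, so the loss is moderate. This stands, and it rules out several stronger readings that a reader might infer.

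- *That the trial has only 22–25% controls and about 22–29% power.* Those figures describe the ward-phase contrast in step 6, which Statistical methods does not plan. Entering that control share and an R² of about 0.75 into the power routine would give HR 1.67–1.70, far too pessimistic for the planned model.
- *That nothing can be learned after month 9.* No ward is in its control phase for the last 15 of 24 months, but unexposed patients and person-time continue.
- *That clustering lowers power further.* Ward indicators already absorb constant ward effects, and the article gives no basis for a ward-by-time correlation.
- *That 20% means HR 1.20.* This would need about 945 events, or about 1,350 patients, even at an even split. It does not reproduce the stated figure, and the Sample size section gives no hazard ratio. It shows only that the conversion should be written down.

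It is also fair that the even split and zero correlation are inferred, that the full protocol may hold the options used, and that the usual gap is 3–6 percentage points from 'approximately 20%'. None of this restores 80%. Even with the 48-hour rule ignored, the most favourable case examined (1,000 patients, half reviewed, ward shares 50/25/15/10) reached about 77%.

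**Conclusion.** The point holds for the planned time-varying model. The stated 80% power at about 20% is not delivered by the design described in the same article. Power at HR 1.25 is about 43–64% with 900 patients and 46–68% with 1,000, and the detectable reduction is about 23–30%.

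This rests on assumed review rates of 40–95%, assumed ward shares of 40/25/20/15, and a constant hazard for the conversion to length of stay. The direction did not depend on the review rate or ward mix: no case examined reached 80%. Part of the power that remains comes from comparing reviewed with unreviewed patients on switched wards, rather than from the contemporaneous ward comparison that Study design gives as an advantage.

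This should be fixed, but it is not critical. The sample is fixed, 582 patients were already enrolled, no estimate or error rate depends on the sentence, and the reported confidence intervals will limit misreading of a null result.

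**What to change.** Replace the sentence with the minimum detectable hazard ratio for discharge under the planned analysis, by simulation or with the Stata routine already named. Specifically:

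- Use the expected as-received exposed share among discharges after 48 hours, and the R² of that exposure, not of ward phase, on ward and quarter.
- Show the range over 800–1,000 patients and plausible review rates, with the assumed ward shares stated.
- Describe the result as the smallest effect detectable at 80% power and drop 'up to'.
- State the conversion from hazard ratio to length of stay, for example 1 − 1/HR under a constant hazard. The Antimicrobial stewardship section equates HR 1.16 with a 16% reduction, whereas this conversion gives 1 − 1/1.16 = 13.8%.
- If the ward-phase contrast is reported, label it as a lower bound.

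The cost is one rewritten paragraph and a less favourable figure. No extra patients and no change to the analysis are needed.

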### Recruitment

All consecutive immune-competent adult patients admitted to a hospital ward with a diagnosis of CAP will be enrolled in the study, to ensure maximum enrollment.

### Assignment of intervention

Given the ‘naturally’ blinded allocation process of patient admission to one of four medical wards, the pressure to demonstrate an early impact to administrators and the ethical principle of utilitarianism, the ASP-i will first be implemented in the medical ward most likely to accommodate the majority of CAP patients. The remainder of the wards will be sequentially introduced to the ASP-I in order from the ward most likely to care for the most to that most likely to care for the least number of CAP patients, based on historical admission patterns.

### Blinding

It is not possible to blind the ASP members or the attending physicians to the ASP-i. The ASP members are not blinded to the outcome assessment, but this should have minimal risk of bias, given the objective nature of the primary and secondary outcome measures. The principal investigator is also responsible for data analysis, given the absence of biostatistical expertise at the hospital, the absence of funding to support external biostatistical services, and the need to create quarterly reports for the hospital administrators, as required by the employment contract between the Royal Victoria Regional Health Centre and the principal investigator.

### Data collection

All patient-level data will be extracted from the patients’ electronic medical records by the ASP members, using a standardized electronic data collection form that is accessible on a portable tablet computer. The elements of the data dictionary defining the variables and instructions for data abstraction have been preprogrammed into each variable’s respective field and can be accessed at the point of care by touching the field name. Other techniques to ensure internal validity of the data include preprogrammed data integrity constraints, such as range checking and logical data edits and predefined value lists in drop-down menus for the vast majority of data elements. Summary descriptive statistics for all continuous variables will be calculated within each patient record to permit real-time review, to identify any potential outlying values. The external validity of the data will be assessed by an external reviewer on a biannual basis using a random sample of 10 % of the database. The data elements that will be audited by the external reviewer include only those elements that are included as either outcomes or covariates in the final statistical model and are feasible for validation against an objective source. Access to patient-level data is restricted to ASP members. All patient-level data will be protected according to the Personal Health Information Protection Act of Ontario regulations [33].

### Statistical methods

An extended Cox regression analysis that models the ASP-i as a time-variant covariate will be used to compare the primary and secondary outcome measures between the control and intervention groups [34]. Violations of the proportional hazards assumption for each covariate will be identified using the method of Schoenfeld residuals combined with the graphical method of log-log survival curve analysis [34]. Results will be reported as hazard ratios with 95 % confidence intervals. Patients who remain in hospital beyond 14 days will be administratively censored. Competing events, such as death or transfer from a medical ward to a critical care unit will be assumed to be non-informative conditional on the covariates included in the final model [34]. Time to ASP-i will be modeled as a time-variant covariate in the final model to account for any time-dependent bias [23]. The ASP-i exposure will be coded as a dichotomous variable; 0 = no ASP-i, switching to 1 = ASP-i at the time of the ASP-i and remaining 1 throughout the remainder of the follow-up time. This method treats a patient who has received an ASP-i as a non-ASP-i patient prior to the intervention. Other variables known to be associated with the primary and secondary outcome measures will also be included in the final model [5], and include; age, sex, Charlson comorbidity index, CURB-65 score, time (days) to clinical resolution, and complications from pneumonia, such as empyema. Fixed effects of wards on the outcomes will accounted for by including them as indicator variables in the final model. Maturation of ASP-i effect on outcomes over time will be adjusted by including a categorical time variable in the final model (time variable will be defined as ‘quarter’ from start of study). A dichotomous variable for acceptance or rejection of the ASP-i will be part of an interaction term with the control/intervention group variable to permit a per-protocol analysis. Sensitivity analysis will be done using a competing events Cox regression model to determine the impact of the assumption of the non-informative nature of events, such as death and admission to an intensive care unit [35].

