
### Outcome measures

The primary outcome measure is length of hospital stay, measured in minutes from the documented time of admission to the documented time of discharge (or censoring). These times are determined and entered into the patient’s electronic medical record by bed allocation staff who are blinded to the intervention. The secondary outcome measures are days and duration of antibiotic therapy. The start and stop dates corresponding to antibiotic administration while the patient is admitted to hospital are entered into the patient’s electronic medical record by pharmacy assistants who are blinded to the intervention. All inpatient antibiotic administration is verified through the paper-based medical administration record by a pharmacy assistant blinded to the intervention. The number of days of antibiotic therapy is defined as the total number of days of all antibiotics administered to the patient both while in hospital and after discharge. The duration of antibiotic therapy is defined as the number of days that the patient received antibiotics both while in hospital and after discharge. For example, if a patient received two antibiotics for 4 days over the same time period, then the days of antibiotic therapy is 8 days and the duration of antibiotic therapy is 4 days. The relevance of collecting both days and duration of therapy is that days of therapy is considered a valid metric for monitoring and comparing antibiotic utilization both within and across hospitals, whereas duration of therapy is necessary for determining adherence with best-practice treatment guidelines [30]. All antibiotic data from discharged patients will be extracted (by LM or GD) from the physician discharge summary and all patients will be contacted 30 days after discharge to verify their adherence with the prescribed antibiotic record from the discharge summary. Other secondary outcome measures include inadvertent adverse outcomes of readmission and mortality 30 days after discharge from hospital. Readmission to hospital is determined through telephone survey with the patient and verification through the Royal Victoria Regional Health Centre patient database. Survival is determined through telephone survey with the patient. The status of patients who cannot be reached by telephone will be verified through the Ontario vital statistics registry.

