### Participant timeline

Enrollment of patients started 1 April 2013. The study is expected to enroll patients until 31 March 2015. All consecutive patients who meet the inclusion criteria and have no exclusion criteria will be eligible for the intervention. The ASP-i intervention may be implemented any time from 48 hours after admission in those patients who meet the criteria for ASP review. All patients who have not experienced an outcome measure at 14 days after admission will be censored from the study. Patients who die or are transferred from the ward (to the intensive care unit or other hospital) will also be censored. Patients who are discharged from hospital and are not censored will be contacted 30 days after discharge to determine their adherence with antibiotic prescription (if relevant), survival status, and readmission status.

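### Days of antibiotic therapy is a sum over drugs, not a time since admission, so the extended Cox model assigned to it puts outcome and exposure on different scales

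*Protocol article*

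**What the plan says.** All places are in the protocol article, under Methods/Design.

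- **Outcome measures** names the outcome: "The secondary outcome measures are days and duration of antibiotic therapy". It then defines it: "The number of days of antibiotic therapy is defined as the total number of days of all antibiotics administered to the patient", counting treatment in hospital and after discharge. For two drugs given over the same 4 days, "then the days of antibiotic therapy is 8 days and the duration of antibiotic therapy is 4 days".
- **Statistical methods** assigns the model: an extended Cox regression with a time-varying ASP-i "will be used to compare the primary and secondary outcome measures between the control and intervention groups". The ASP-i indicator starts at 0, "switching to 1 = ASP-i at the time of the ASP-i and remaining 1 throughout the remainder of the follow-up time". Results are to be hazard ratios with 95% confidence intervals.
- **Participant timeline** puts the ASP-i at any time from 48 hours after admission. It also counts the 30-day contact from discharge.

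The article gives no separate time axis for days of therapy, no rule for placing the switch on that axis, and no other final analysis for this outcome.

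**The concern.** A Cox model with a covariate that switches during follow-up needs the event and the switch on one axis. Length of stay meets this, because discharge and ASP-i are both timed from admission. Duration of therapy meets it closely if treatment starts at admission and is unbroken. Days of therapy does not: a patient on two drugs moves two units along the outcome axis for each day lived.

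The article's Discussion presents the time-varying coding as its remedy for counting unexposed time as exposed. For days of therapy, a switch entered in elapsed days brings that misassignment back. Days of therapy appears in the research question and is the metric the article itself calls valid for comparing antibiotic use within and across hospitals, so a misleading hazard ratio would matter.

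A second, smaller point concerns 30-day death and readmission. Their clock starts at discharge, when ASP-i status is already fixed, so time-varying coding gives no protection there. The ASP-i group can contain only patients who stayed at least 48 hours.

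**Working it through.** **1. The plan's own figures.** The only figure given for this outcome is the example: 2 drugs × 4 days = 8 days of therapy, against a duration of 4 days. It reproduces, and it shows that the two measures differ by the number of concurrent drugs. The design calculation (about a 20% reduction) concerns length of stay only. With 70% events among 800 to 1,000 patients (560 to 700 events) and an assumed exposed share of one half, the detectable hazard ratio is exp[(1.960 + 0.842)/√(events × 0.25)] = 1.267 to 1.236, or 0.789 to 0.809 inverted. That figure is not touched by this point.

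**2. The two scales at the earliest ASP-i.** At 48 hours, a patient on two drugs from admission has lived 2 days and accrued 2 × 2 = 4 drug-days. A switch entered at 2 on the drug-day axis marks units 2 to 4 as exposed, although they accrued before the ASP-i.

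**3. Illustration at 60 hours.** The 60-hour review, the number of drugs and the unscaled switch are assumptions, not figures from the article.

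| Drugs from admission | Drug-days before review | Counted as exposed | Share |
|---|---|---|---|
| 2 | 2 × 2.5 = 5 | 5 − 2.5 = 2.5 | 50% |
| 3 | 3 × 2.5 = 7.5 | 7.5 − 2.5 = 5 | 67% |

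These shares describe one hypothetical patient. They are not a bias in the hazard ratio.

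**4. Simulation with no true effect.** All inputs are assumed: 900 patients; course length 0.5 days plus a gamma variable with mean 7 days; 60% of patients on intervention wards; ASP-i uniform between 2 and 5 days among those still on antibiotics; one or two drugs throughout; no censoring; 40 to 100 replicates. Values are good to about 0.02. The correct hazard ratio is 1.

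| Share on two drugs | Duration, elapsed time | Days of therapy, switch in elapsed days | Days of therapy, switch in drug-days |
|---|---|---|---|
| 0% | 0.98 | 0.98 | 0.98 |
| 25% | 1.00 | 0.955 | 1.235 |
| 50% | 0.98–1.00 | 0.89–0.91 | 1.27–1.30 |
| 75% | 0.98 | 0.83 | 1.17 |

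With the switch in elapsed days, two-drug patients collect exposed units in which they could not have finished, which pulls the ratio below 1. With the switch in drug-days, one-drug patients reach it at a lower count and also finish at a lower count, which pushes the ratio above 1. With half of patients on two drugs, a nominal 5% test rejected in 27% of replicates (elapsed days) and 98% (drug-days). Comparing mean days of therapy by ward allocation gave ratios of 1.01 to 1.02. Allocation was independent of outcome, so the expected ratio is 1 and the excess is simulation noise.

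**The case against.** The strongest reply is that the article does not say on which axis the switch would be entered for days of therapy, so any stated bias belongs to one unstated implementation. That stands for size and direction: the results above go below 1 under one choice and above 1 under the other, and they are small if few patients take two drugs. It does not rescue the assignment, because neither choice gave a ratio of 1 once some patients took two drugs. Adjusting for the number of drugs is not in the listed model. It would also be doubtful, since discontinuing antibiotics and changing the spectrum are among the possible recommendations, so the rate of accrual is itself something the ASP-i may change.

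It may also be said that such detail belongs in an analysis plan not shown. But the article does not leave the model open. It assigns one to this outcome.

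Three stronger readings are tempting, and the article does not support them.

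- A reader might infer that the 14-day rule cuts off high drug-day totals, such as two drugs for 8 days scoring 16. The rule reads "All patients who have not experienced an outcome measure at 14 days after admission will be censored from the study", and Statistical methods applies it to patients still in hospital. It is hospital time since admission and does not cap a drug-day total.
- A reader might infer that courses ending after discharge and beyond day 14 are cut. The definition counts treatment after discharge, and the 30-day contact checks it.
- A reader might infer that the 30-day comparisons simply set long stays against short ones. This is only a tendency: controls include patients of every length of stay, and the model adjusts for severity and comorbidity. The LACE-adjusted relative risks under Monitoring already compare 30-day events, but as a safety trigger and not as the final analysis.

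**Conclusion.** The point holds for days of antibiotic therapy. The article defines this outcome as a sum over drugs and assigns it a model whose exposure switches in elapsed time, and nothing elsewhere reconciles the two. The hazard ratio would have no valid interpretation. That conclusion needs only the article's definition, its example and its model assignment. The magnitudes (50% and 67% of pre-review drug-days; null hazard ratios of roughly 0.83 to 0.96 or 1.17 to 1.30 with 25% to 75% of patients on two drugs) rest on assumed drug mix, timing and implementation, and should be read as illustrations.

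Length of stay is unaffected and duration of therapy largely so. This is therefore a change that should be made to a secondary analysis, not a threat to the primary result. The 30-day point is subsidiary and was reasoned from the text, not simulated: time-varying coding cannot help once status is fixed at discharge, and the 48-hour condition selects the ASP-i group.

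**What to change.** In Statistical methods:

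1. Limit the extended Cox model with time-varying ASP-i to length of stay and duration of therapy, the latter defined as time to stopping antibiotics.
2. Analyse total days of therapy as a count or mean (negative binomial or quasi-Poisson), reporting a ratio and a mean difference with 95% confidence intervals. Define exposure by ward rollout period and adjust for ward, calendar quarter and baseline covariates.
3. Report 30-day death and readmission as 30-day risks by ward rollout period.

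Moving only the switch onto the drug-day scale is not a sufficient repair.

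The change is mainly one of wording, with three costs to state. First, the estimand becomes the effect of rolling the program out on a ward, not of receiving a review. Second, precision may fall. If the first ward starts after month 3 and the others follow every 2 months, the last starts after month 3 + 3 × 2 = 9, so no unexposed ward remains for the rest of the 24 months. Third, data may be incomplete. Participant timeline limits the 30-day contact to patients discharged and not censored, so full-course antibiotic data and 30-day status may be missing after death, transfer or a stay beyond 14 days. The report should say how many patients this affects.
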